## Abstract

**Summary:**

This feasibility study for a future definitive randomized trial assesses the use and acceptability of a new clinical decision tool to identify risk of a vertebral fracture and those who should be referred for spinal radiography in women aged 65 or over presenting to primary care with back pain.

**Purpose:**

Approximately 12% of older adults have vertebral fragility fractures, but currently fewer than one-third are diagnosed, potentially limiting access to bone protection treatment. Vfrac is a vertebral fracture screening tool which classifies individuals into high or low risk of having a vertebral fracture, allowing targeting of spinal radiographs to high-risk individuals. The objective of this study was to investigate the feasibility of conducting a cluster randomized controlled trial to evaluate the use of an online version of Vfrac in primary care.

**Methods:**

The study will run in six general practices, with three given the Vfrac tool for use on older women (> 65 years) consulting with back pain and three using standard clinical processes for managing such back pain. Anonymised data covering a 12-month period will be collected from all sites on consultations by older women with back pain. Focus groups will be undertaken with healthcare professionals and patients on whom the tool was used to understand the acceptability of Vfrac and identify factors that impact its use. These patients will be sent a paper version of the Vfrac questionnaire to self-complete at home. Outputs of the self-completion Vfrac (high versus low risk) will be compared with the face-to-face Vfrac (high versus low risk), and agreement assessed using Cohen’s kappa.

**Results:**

This study will evaluate the use and acceptability of Vfrac within primary care and determine if data on resource use can be collected accurately and comprehensively.

**Conclusions:**

This article describes the protocol of the Vfrac feasibility study.

**Trial registration:**

ISRCTN18000119 (registered 01/03/2022) and ISRCTN12150779 (registered 10/01/2022).

## Background

There are approximately 3.5 million people in the UK living with osteoporosis [1] and more women are affected with this condition than men, with 1 in 2 women over the age of 50 breaking a bone because of it [2]. Vertebral fragility fractures (VFFs) are of particular importance, as they identify people at a high risk of future fractures, which can lead to morbidity, disability and reduced health-related quality of life [3, 4]. Treatment with bone protection therapies are available to reduce the risk of further fractures by 30–70% [5, 6]. The problem is that many patients fail to receive a diagnosis of VFFs, with estimates suggesting that over two-thirds remain undiagnosed [7]. There are many reasons for this important healthcare gap, including lack of clinical signs specific to vertebral fracture, the high prevalence of all-cause back pain in older people, and difficulty in understanding who should have spinal X-rays.

To address this, we have developed the Vfrac clinical decision tool to help primary healthcare practitioners decide if an older woman with back pain is at high risk of a VFF and therefore requires a spinal radiograph to confirm the diagnosis. Vfrac is targeted for use during consultations between a healthcare professional and an older woman consulting with back pain. Vfrac is the only evidence-based decision tool developed from research involving women with and without VFFs including qualitative[8], cross-sectional [9–11] and case–control studies [12]. The Vfrac tool comprises 15 questions based on self-reported data and a physical examination and takes approximately 5 minutes to perform. It has been made available on a web-based online interface to make it accessible for use across different IT systems in primary care in the UK. Use of the pre-determined cutoff [13] produces the output (“low risk—spinal X-ray is not recommended”—or “high risk—spinal X-ray is recommended as may have a vertebral fracture”). As previously published [14], the Vfrac clinical tool has an area under the curve (AUC) of 0.802 (95% CI 0.764–0.840). Statistical modelling shows no evidence of over/underfitting; optimism in the estimate of the AUC was 0.019 estimated using 500 bootstrapped samples; and multiple imputation to account for the missing data produced results that were similar to our final model and provides internal validation. A pre-trial economic evaluation, also published [14], calculates the incremental cost-effectiveness ratio (ICER) for Vfrac compared to standard care is £17,000 per QALY and Vfrac has the potential to be cost-effective but a definitive trial is warranted.

Prior to this study, no testing of Vfrac has been undertaken within a real-world clinical setting and this is necessary to understand if and how it will be used, and whether changes to the tool are required to optimise its use. Primary care service delivery has changed in the face of the COVID-19 pandemic, and it is unlikely that there will be a full-scale return to face-to-face consultations with GPs as the primary mode of clinical assessment. This warrants an investigation as to whether the Vfrac tool can be used remotely by patients, and this is the first aim of this feasibility study. Specifically, to assess whether patients can self-complete the questionnaire at home and whether the results will be in agreement with the use of the Vfrac tool by healthcare professionals in primary care. The second aim of this study is to investigate the acceptability of Vfrac as an online clinical decision tool in primary care, as this will help identify barriers and facilitators to its implementation and delivery for the design of a future definitive trial of Vfrac.

## Methods

### Feasibility study design

A screenshot of the online Vfrac tool is given in Fig. 1. Vfrac is a multicentre feasibility study, with nested evaluations. There are three work packages (WP), the objectives of which are summarised in Table 1. An overview of the study processes in each of the work packages is provided in Fig. 2**.**

**Fig. 1 Fig1:**
[figure not shown]
The online vertebral fracture screening tool made available for use by general practitioners in three general practices across the West of England Clinical Research Network

**Table 1 Tab1:** Work packages of the Vfrac feasibility study

Work Package (WP)	Vfrac study component	Objective(s)
1	Vfrac implementation within primary care	To optimise integration of the Vfrac decision tool within primary care IT systems and clinical pathways. To determine the length of follow-up (from assessment to final management) that is required for a future trial.
2	Nested qualitative assessment of acceptability of the Vfrac tool	To understand how acceptable Vfrac is to healthcare professionals (providers) and patients (recipients) and identify factors that impact on implementation, including barriers and facilitators to delivery
3	Nested assessment of agreement between the use of Vfrac within general practices and self-completion at home	To decide whether Vfrac can be self-completed at home or whether it needs to be delivered face-to-face for any future trial.

**Fig. 2 Fig2:**
[figure not shown]
Overview of study processes for each of the three work packages of the Vfrac feasibility study

### Regulatory approvals

Ethics approval was obtained from Yorkshire & The Humber—Bradford Leeds Research Ethics Committee on 28th June 2022 (reference 22/YH/0135) and Health Research Authority approval on 28th June 2022. The study is registered on the International Standard Randomised Controlled Trial Number registry (the ISRCTN reference covering work packages 1 and 2 is ISRCTN18000119 and work package 3 is covered by the ISRCTN reference ISRCTN12150779).

### Patient and public involvement (PPI) in study design and delivery

The design of this feasibility study has been actively discussed with our Patient Experience Partnership in Research group (PEP-R), to seek their views and thoughts, and to modify our processes and strategies as necessary. To date, seven members of the PEP-R group have contributed to the study design—in particular, our recruitment strategies, conduct of the patient interviews and focus groups, the development of all patient-facing materials to improve wording and readability, and some administrative changes. PPI in our governance structure is also key; two people with osteoporotic vertebral fractures have agreed to take an active part in our Steering Committee, which will meet every 6 months.

## WP 1: Vfrac implementation within primary care

For this work package general practices will be recruited and then assigned to either intervention or control by purposeful selection to ensure there is variation in practice size and deprivation levels in both groups. Six general practices will be recruited from the West of England region purposively, to include small and large practices and practices within different Primary Care Networks (PCNs)/clusters, which vary in deprivation as assessed by the Index of Multiple Deprivation. General practices will be approached by the West of England Clinical Research Network, which covers the Integrative Care Boards of: Bristol, North Somerset and South Gloucestershire; Bath and North East Somerset, Swindon and Wiltshire; and Gloucestershire. Using a proforma, baseline data will be collected from all six practice managers to describe their practice (Table 2).

**Table 2 Tab2:** Data collection from six general practices recruited to the Vfrac feasibility study

**Feasibility study of Vfrac implementation within primary care**	**Outputs**
Outcome measures from intervention and control practices 1.1 Descriptives of each practice -Number of registered patients -Number of women ≥ 50 and ≥ 65 -Computer system -Name of PCN/cluster -Other demographic characteristics 1.2 Type of healthcare professional carrying out initial consultation for back pain 1.3 Number and date of consultations by older women with back pain 1.4 Resource use after initial consultation for back pain including -Consultations in primary and secondary care -Referrals including rheumatology, osteoporosis clinics, geriatrics, physiotherapy, pain clinic -Investigations including DXA, radiology -New medication prescriptions 1.5 New diagnoses since initial consultation for back pain Additional outcome measures from intervention practices only: 1.6 Proportion of consultations for back pain where Vfrac was used 1.7 Other consultations where Vfrac was used 1.8 Results of the Vfrac tool completed in primary care	1. Training requirements for healthcare staff 2. IT requirements and options for ideal integration within IT systems 3. Options for ideal integration within clinical pathways 4. Required length of follow-up for any future definitive trial to capture most (> 90–95%) patient journeys 5. Contribution to understanding of ‘usual care’ for patients who consult with back pain in the control practices where Vfrac is not used

**Nested qualitative assessment of acceptability**	**Outputs**
Outcome measures from participants recruited at intervention practices 2.1 Understanding of acceptability to healthcare professionals and patients 2.2 Identification of factors that impact on implementation, including barriers and facilitators to delivery	1. Results will form the basis of recommendations to modify Vfrac and improve delivery in any future trials

**Nested assessment of agreement between the use of Vfrac within general practices and self-completion at home**	**Outputs**
Outcome measures from participants recruited from intervention practices 3.1 Outputs of self-completion Vfrac 3.2 Satisfaction and ease of the use of self-completion questionnaire 3.3 Participants views of whether they preferred face-to-face assessment in primary care or self-completion at home 3.4 Assessment of agreement between outputs of the self-completed Vfrac and face-to-face Vfrac using Cohen’s kappa	1. Decision as to whether Vfrac can be carried out as a self-completion assessment or whether it needs to be delivered face-to-face for any future trial 2. Summary statistics for proportions of participants satisfied with process, interpersonal and technical attributes will be calculated 3. Recommendations in free-text fields of the satisfaction and ease of use questions will be used to modify the (future) tool if necessary

A clinical update on osteoporosis will be offered to all. Three practices will then be assigned to the intervention arm and three to the control by purposeful selection to ensure there are both large and small practices in both groups that have varying levels of deprivation. The control practices will use standard clinical processes for older women consulting with back pain. Those in the intervention arm will be trained in the use of Vfrac and will have it made accessible from their IT systems (through provision of a URL via pop-ups on typing relevant words such as back pain). The use of the Vfrac tool will be encouraged within their clinical pathways for management of older women (over 65 years of age) who consult with back pain. The use of the tool in a manner that is in accordance with each practice’s service delivery model will be facilitated by the research team in discussion with the clinical team. As the use of Vfrac poses only minimal/no risk, the use of a waiver of consent by individual patients for this cluster-level intervention is appropriate [15].

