### Follow-up

Regular data will then be collected on consultations by older women with back pain from all six general practices every 3 months for 12 months. Data will be collected by electronic download to capture type of healthcare professional carrying out initial consultation for back pain, number and date of consultations by older women with back pain, resource use after initial consultation for back pain and new diagnoses since initial consultation for back pain (Appendix 1). In addition, from intervention general practices data will be collected on proportion of consultations for back pain where Vfrac was used, other consultations where Vfrac was used, and results of the Vfrac tool recorded in the medical notes (Appendix 2). Data collected will be anonymised at each general practice to remove patient identifiable details such as name, address and NHS number.

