**Table Taba:**

Anonymised ID
Date of birth
Date of initial consultation for back pain *{now called initiating event}*
Details of initiating event
Professional grouping of healthcare worker carrying out initiating event, e.g. doctor, nurse, and first contact physio
List of other consultations within general practice since initiating event
Medications at time of initiating event
Changes in medications since initiating event—with date of change
Referrals to secondary care since initiating event—with date of referral
Radiology referrals since initiating event—with date of referral
DXA referrals since initiating event—with date of referral
Diagnoses since initiating event—with date of diagnosis

*Patient level data to be anonymised by general practices before returning to research team.

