**Table Tabb:**

Anonymised ID
Date of birth
Date of initial consultation for back pain *{now called initiating event}*
Details of initiating event
Professional grouping of healthcare worker carrying out initiating event, e.g. doctor, nurse, and first contact physio
Vfrac unique code (watermark)
Output of Vfrac (recommend X-ray; no X-ray recommended; value)
List of other consultations within general practice since initiating event
Medications at time of initiating event
Changes in medications since initiating event—with date of change
Referrals to secondary care since initiating event—with date of referral
Radiology referrals since initiating event—with date of referral
DXA referrals since initiating event—with date of referral
Diagnoses since initiating event—with date of diagnosis

*Patient level data to be anonymised by general practices before returning to research team.

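### Outcome 1.4 promises secondary-care consultations and investigations, but the Appendix 1 and 2 download forms record only general-practice contacts and dates of referral for these items

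*Protocol article*

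**What the plan says.** Outcome 1.4 in Table 2 (section WP 1) defines resource use after the first back-pain consultation under four items: "Consultations in primary and secondary care", referrals, "Investigations including DXA, radiology", and new prescriptions. Referrals are thus a separate item from both consultations and investigations.

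The Follow-up section says that the electronic download, taken every 3 months for 12 months at all six practices, captures "resource use after initial consultation for back pain and new diagnoses since initial consultation for back pain (Appendix 1"), with Appendix 2 for the additional items from intervention practices. The appendices are the follow-up data collection forms. Each asks for "List of other consultations within general practice since initiating event". For the rest of the pathway, each asks for "Referrals to secondary care since initiating event—with date of referral", "Radiology referrals since initiating event—with date of referral" and "DXA referrals since initiating event—with date of referral". Each also asks for baseline medication, dated medication changes and dated diagnoses. Appendix 2 adds the Vfrac code and output.

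The WP1 objective in Table 1 includes: "To determine the length of follow-up (from assessment to final management) that is required for a future trial". Output 4 in Table 2 makes this the follow-up needed to capture more than 90–95% of patient journeys. The Discussion sets a stop/go limit of 15 months on it.

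**The concern.** Two parts of the article disagree on what is collected. Table 2 names contacts with secondary care and investigations as outcomes. The forms that are their source record that a woman was referred and when, but not whether she was seen or scanned, or on what date.

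Two stated purposes depend on these fields. The first is to judge whether resource-use data can be collected fully and correctly for a later cost-effectiveness estimate (Abstract, Results; Discussion). A form without a field for secondary-care consultations cannot test whether they can be collected. The second is to time the journey from assessment to final management. The tool's high-risk output is a recommendation for a spinal X-ray, yet the forms have no field showing whether or when that X-ray took place.

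**Working it through.** The plan states no figure to reproduce here, so the check is a field-by-field match of Table 2 against Appendices 1 and 2.

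| Table 2 item | Field on both forms | Match |
|---|---|---|
| 1.4 primary-care consultations | Other general-practice consultations after the initiating event | Yes |
| 1.4 secondary-care consultations | None (referral and its date only) | No |
| 1.4 referrals | Secondary-care referrals, dated | Yes |
| 1.4 investigations (DXA, radiology) | DXA and radiology referrals, dated; no date performed | Requests only |
| 1.4 new prescriptions | Medication changes, dated | Yes |
| 1.5 new diagnoses | Diagnoses, dated | Yes |
| Output 4, end of journey | No dedicated field; diagnosis and medication dates usable | In part |

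**Other sources in the article.**
- The online tool stores answers, score, submission date and code. It holds nothing about what happened afterwards.
- Radiology records are accessed in WP3, but for WP3 patients from the three intervention practices and to establish presence or absence of vertebral fracture.
- The Clinical Practice Research Datalink work described in the Discussion uses national data, not records from these six practices.

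None of these supplies the missing items for all six practices.

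**Four journeys as the forms would record them.**
1. Referred, X-rayed, fracture diagnosed, treatment changed: the diagnosis and medication change are both dated, so an end point exists.
2. Referred, X-rayed, no fracture, no medication change: the last dated pathway event is the radiology referral.
3. Referred, never X-rayed, no new diagnosis or medication change: the record shows the same pathway fields as journey 2.
4. Referred to a clinic, seen and discharged with no new diagnosis or medication change: the last dated pathway event is the secondary-care referral.

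**Direction of the error.** Suppose an analyst closes journeys 2 and 4 at the last dated pathway event. Then recorded time = time to referral, while true time = time to referral + wait, with wait ≥ 0. Recorded time never exceeds true time. Replacing some journey times by equal or smaller values cannot raise any percentile, so the time that captures 90–95% of journeys can only stay the same or fall. It falls if enough of the affected journeys lie in the upper tail.

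**Size.** This needs the share of journeys of types 2 and 4 and their waits. The article gives neither, so no figure can be put on the shift or on its effect against the 15-month limit.

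**The case against.** The strongest reply is that the forms hold more than referrals and general-practice contacts. A reader might infer that they hold nothing else, or that final management cannot be dated at all. Neither is right. Both forms record dated diagnoses and dated medication changes, and for a pathway meant to find fractures and start bone protection these are natural end points. Later general-practice consultations are also listed and may sometimes show when a result was discussed. This narrows the timing problem to journeys that end without a new diagnosis or medication change.

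A second reply is that Table 2 says investigations, not investigations performed, and a dated request captures these in part. That is fair. But Table 2 lists referrals as a separate item, so a referral cannot stand in for both. Table 2 promises neither body site nor a coded imaging result, so their absence breaks no commitment and is not part of this point.

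A third reply is that a journal article condenses the full protocol. That covers an operational definition of final management and field-level coding, and neither is held against the plan here. It does not cover the forms themselves, which are reproduced with an explicit list of the data to download and disagree with Table 2.

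Finally, a reader might assume a wait, say 1 to 6 months, and take it off the follow-up estimate. The documents give no waiting times. Such a wait would apply only to the affected journeys and would not carry over one for one to the 90–95% point.

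**Conclusion.** The point holds in this form. Of the four resource items in outcome 1.4, half of one (the secondary-care part of consultations) is not collected, and another (investigations) is collected only as requests. The study as written cannot report secondary-care consultations, and cannot show whether they could be collected in a future trial.

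For journeys that end in a scan or clinic visit without a new diagnosis or medication change, there is no dated investigation or clinic end point. This may understate output 4 and make the 15-month criterion easier to meet. The direction assumes that such journeys are closed at their last dated pathway event, and the size cannot be established from the documents.

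It would go too far to say that the two purposes fail. General-practice contacts, referrals, requests, prescriptions and diagnoses are all collected, so both questions remain partly answerable. The conclusion assumes that the appendices are the complete download list, which is how they are presented.

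**What to change.** Add to both forms:
- the date performed for radiology and for DXA;
- the date of each secondary-care attendance or, failing that, of the clinic letter.

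Use these dates together with the dated diagnoses and medication changes to time the journey for output 4.

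If practices cannot export attendances, restrict outcome 1.4 to referrals for secondary care, and report that the future trial needs another source for secondary-care use. That would itself be a useful feasibility result.

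The cost is a few extra fields in the electronic search at six practices and a revised form. Recruitment began in September 2022, so the new fields may have to be filled retrospectively at a later quarterly download. That assumes that the practice records hold these dates and that each practice can still match its anonymised IDs to its records.
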